#### Triangulation study analysis

We will compare data collected directly from the participants with that obtained from routinely collected data recorded on computerised patient records. There are discrete variables such as number of GP visits, number of hospital visits etc. as well as continuous variables such as medication and associated costs that will be compared for consistency. This comparison will be completed using the intraclass correlation coefficient (ICC) with a value of above 0.7 showing good consistency between the two data sources.

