#### Interventions

An ‘enhanced rehabilitation’ intervention will be compared with usual rehabilitation care. Usual care consists of a multi-disciplinary rehabilitation delivered by the acute hospital, community hospital and community services depending on patients’ individual needs at different times during their recovery and on the availability and accessibility of services in different areas. The multidisciplinary team delivering care and rehabilitation includes orthopaedic surgeons, orthogeriatricians, nurses, physiotherapists, occupational therapists, dieticians, pharmacists, general practitioners (GPs) and social workers. The settings for care include acute orthopaedic or orthogeriatric wards, rehabilitation units in community hospitals, rehabilitation beds in care homes, the patient’s own home and care home settings all delivered by a variety of community teams in both health and social care services.

The main aim of the intervention is to enhance usual rehabilitation by increasing the amount and quality of patients’ practice of physical exercise and activities of daily living in order to improve their functional outcomes at the 3-month follow up. We also hypothesise that improving patients’ self-efficacy will increase their motivation to engage in the rehabilitation process, improve the quality and quantity of this practice and increase their engagement.

We will endeavour to enhance rehabilitation self-efficacy [22] by means of a patient-held information workbook and goal-setting diary given to the participant in the acute hospital which they will keep throughout the follow-up period of the study. Six additional therapist/technical instructor sessions will be available to patients once they return home or are admitted permanently to a care home. These extra sessions will be tailored to individuals’ needs at the discretion of the community occupational therapist or physiotherapist responsible for their care in liaison with the therapists allocated to deliver the extra sessions.

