#### Delivery of the intervention

The intervention will be delivered by the therapists and their assistant staff employed by BCUHB. The therapy service managers in BCUHB have agreed to organise the extra sessions for patients in the intervention arm of the study, which will be funded by NHS excess treatment costs. The extra six sessions of rehabilitation will be delivered by additional physiotherapists and therapy assistants. This will be done in collaboration with the existing therapists delivering the usual care. The intervention therapy teams will be alerted to which group the patient is randomised and will arrange a time for an initial assessment and goal-setting session to visit the patient in the acute hospital or in a community setting. The remaining five sessions will be used according to individual’s need and the individual’s rehabilitation plan.

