#### Health economic measures

EuroQol EQ-5D (three levels) [37].

This is a patient-completed index of health-related quality of life, which gives a weight to different health states. It consists of five dimensions: mobility, self-care, usual activities, pain/discomfort, and anxiety/depression. Each has three possible responses. The responses record three levels of severity (no problems, some/moderate problems and extreme problems) which is then converted to a health utility weight using UK norms. It will be used at baseline and at the 3-month follow-up assessment and allows the calculation of quality-adjusted life years (QALYs), using area under the curve method which will be used as part of the economic analysis.ICEpop CAPability measure for Older people [38,39].

This is a patient-completed measure of capability in older people that focuses on well-being rather than health. It comprises five attributes: attachment (love and friendship); security (thinking about the future without concern); role (doing things that make you feel valued); enjoyment (enjoyment and pleasure); and control (independence). Each attribute has four possible responses. The responses record the extent of capability (all, a lot, a little, and none), and the five-digit outcome is converted to capability utility derived from UK norms. It will be used at baseline and at the 3-month follow-up assessment as part of the economic analysis.Client service receipt inventory (CSRI) [40].

The CSRI is a questionnaire for collecting retrospective information about study participants’ use of health and social care services, including voluntary services (e.g. charity services), including the components of the rehabilitation programme. This information will be combined with national sources of reference unit costs [41,42] in order to calculate health and social care service costs for the economic evaluation. It will be used at baseline and at the 3-month follow-up assessment as part of the economic analysis.Discrete choice experiment [43,44].

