#### Therapist process outcomes and use of the intervention workbook

In order to describe the rehabilitation programme in both arms of the feasibility study, we will access routinely collected data that therapists complete on their ‘Therapy Manager System’. An information technology manager at BCUHB will extract the following data and return them anonymously to the research team, identifiable only by participants’ study ID. The intervention therapy teams will complete a paper record of how they use the extra sessions which also form part of patients’ clinical records. A BCUHB member of staff will extract the following from these records and return it to the research team:Patient study identification, date of extra session;Whether the session is face to face or indirect;Where the face-to-face session is held; andIf the session is face to face, how much time is spent on different aspects such as assessment, exercise, activity of daily living (ADL) practice and working on the workbook.

We will assess whether the fidelity and dose of the enhanced rehabilitation programme delivered to participants is consistent with our programme theory. We will describe how the programme is delivered along with patients’ views and their use of the workbook which will be collected through focus groups described later. The workbook contains a page of questions and Likert scale type response options to encourage participants to provide feedback on their workbook. Researchers will also collect the diary sections to assess how they are used. We will evaluate engagement with the workbook by counting how many diaries are used, how regularly they are filled out, and whether goals are set and quizzes completed.

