#### Triangulation study of service use information

The health service use data obtained from the patient completed CSRI questionnaires will be compared with the same information obtained from routinely collected data recorded on computerised patient records. The data will be collected by NWORTH and BCUHB IT staff.

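### The service-use triangulation is judged by an ICC above 0.7 without regard to arm, so the two sources can pass while disagreeing on the between-arm difference that a full trial needs

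*Protocol article*

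**What the plan says.** The Triangulation study analysis section sets CSRI responses against data "obtained from routinely collected data recorded on computerised patient records". It names GP visits, hospital visits, medication and associated costs as examples. The comparison is "completed using the intraclass correlation coefficient (ICC) with a value of above 0.7 showing good consistency between the two data sources". The form of the ICC is not given. Neither a mean difference between sources nor any breakdown by arm is mentioned, and all randomised patients enter the triangulation study.

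Four other places bear on what is being compared:

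- Health economic measures: the CSRI covers health and social care use, "including the components of the rehabilitation programme".
- Interventions: "Six additional therapist/technical instructor sessions will be available to patients". Delivery of the intervention describes these as "extra sessions for patients in the intervention arm of the study".
- Therapist process outcomes: "The intervention therapy teams will complete a paper record of how they use the extra sessions". The same section draws routine data for both arms from the electronic Therapy Manager System. It does not say whether the extra sessions are entered there too.
- Study objectives, last item: if the exercise succeeds, electronic records could take the place of patient-reported service use in future studies.

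**The concern.** An ICC measures how much of the total variation lies between patients. When patients differ widely in how much care they use, a sizeable disagreement confined to one arm adds little to the denominator and the coefficient stays high.

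In a full trial, service use matters mainly as a contrast between arms. Two sources that rank patients alike but give different arm contrasts are not interchangeable for that purpose, and the stated criterion does not look at the contrast. The ICC treats the two sources symmetrically, so the weakness is the same whether the records or the patients are at fault.

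Therapist contacts show how such a disagreement could arise here: one source may count the extra sessions and the other may not, in one arm only.

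**Working it through.** The 0.7 is a chosen cut-off, so there is no derived figure to reproduce. The question is what size of one-arm disagreement it lets through.

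**Inputs from the protocol.** Cut-off 0.7. Allocation 1:1. At most g = 6 extra sessions, in the intervention arm only. Target 50 patients (25 per arm). At the 75% retention criterion, 0.75 × 50 = 37.5, about 38 (19 per arm).

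**Assumptions.** The protocol gives no SD of contacts, s, and no underlying agreement, r0 (the ICC if there were no arm gap). Both are shown as ranges.

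**Model.** Patient report P = U + gA + e1 and record E = U + e2, where A = 1 in the intervention arm, Var(U) = s² and each error variance is e². Then r0 = s²/(s² + e²).

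- Var(P) = s² + e² + g²/4, Var(E) = s² + e², Cov(P, E) = s².
- Consistency ICC = 2Cov/(Var P + Var E) = s²/(s² + e² + g²/8).
- Absolute agreement adds the squared overall mean difference, (g/2)², to the sum of variances: ICC = s²/(s² + e² + g²/4).

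With g = 6 the gap adds only 36/8 = 4.5 or 36/4 = 9 to the denominator.

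**SD needed to pass.** With no recording error, s² = 0.7(s² + 4.5) gives s² = 10.5, s = 3.24. For absolute agreement, s² = 0.7(s² + 9) gives s² = 21, s = 4.58. At r0 = 0.9 the thresholds are 3.8 and 5.3; at r0 = 0.8 they are 5.0 and 7.1.

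**Expected ICC, g = 6 (consistency / absolute agreement).**

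| SD of usual contacts | r0 = 1.0 | r0 = 0.9 |
|---|---|---|
| 3 | 0.667 / 0.500 | 0.621 / 0.474 |
| 4 | 0.780 / 0.640 | 0.718 / 0.598 |
| 5 | 0.847 / 0.735 | 0.775 / 0.680 |
| 8 | 0.934 / 0.877 | 0.846 / 0.799 |

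**Simulated chance of exceeding 0.7** (4,000 runs, r0 = 0.9, n = 50):

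- SD 3: 9% / 0%
- SD 5: 89% / 35%
- SD 8: 99.5% / 96%

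At n = 38 the picture is similar (SD 8: 99% / 94%). In every case the sources put the between-arm difference six contacts apart.

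**The reverse error.** At SD 3 and r0 = 1.0 the ICC is 0.667 or 0.500: a fail, although each source is perfect for what it covers.

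**A smaller gap.** With g = 3 and r0 = 0.9 the ICC passes from an SD of about 1.9 (consistency) or 2.7 (absolute agreement).

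**Simpler additions are not enough.** A single overall mean difference would be (6 + 0)/2 = 3, the same as a uniform gap of 3 that leaves the arm contrast intact. Splitting the consistency ICC by arm gives r0 in both arms, because a constant shift within an arm does not alter it.

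**What the arm contrast would show.** Its SE is √(2e² × 2/m) with m per arm. At r0 = 0.9, e² = s²/9.

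- s = 5, m = 25: √(5.56 × 0.08) = 0.67, 95% half-width 1.96 × 0.67 = 1.3.
- s = 8, m = 25: √(14.22 × 0.08) = 1.07, half-width 2.1.
- s = 8, m = 19: 1.22, half-width 2.4.

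A six-contact gap would be plain; a gap of one or two might not be.

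**The case against.** The therapist-contact mismatch is inferred, not stated. The triangulation section says CSRI data are "compared with the same information obtained from routinely collected data recorded on computerised patient records", which on its face is like for like. The variables named are GP visits, hospital visits, medication and costs; therapist contacts come in only through an open-ended list. The extra sessions may also be entered in the Therapy Manager System, and the CSRI's reference to programme components need not mean those sessions. Six is a maximum, because use is tailored to need. All of this stands, so the example is conditional.

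Three stronger readings are tempting and the protocol does not support them.

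- A reader might infer that the paper-record gap biases the economic result. The Economic analysis section costs the programme separately and then adds service-use cost, so leaving the sessions out of the service-use count need not distort the total. Counting them in both places would.
- A reader might infer that the workbook and diary make self-report fuller in the enhanced arm, so that a passing ICC leads to a biased trial. In that case the error lies in the CSRI, the source to be replaced, and a pass would favour the better source.
- A reader might take 0.7 as a binding rule for replacing patient report. The text calls it a sign of good consistency, and the objective is exploratory.

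It can also be said that the ICC form and results by arm are details an article leaves to the analysis plan. That is fair for the form. But the article does fix the method and the cut-off, and that criterion alone does not address the quantity on which replacement depends.

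**Conclusion.** The point holds as a limitation of the stated criterion. An ICC above 0.7, taken without regard to arm, can coexist with disagreement between sources on the between-arm difference, and this does not depend on which source is wrong.

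The size depends on unknowns. For a one-arm gap of six contacts, the expected ICC passes once the SD of usual contacts exceeds 3.2 (consistency) or 4.6 (absolute agreement) with otherwise perfect sources, rising to 5.0 or 7.1 at r0 = 0.8. Below those values the ICC would tend to fail, possibly rejecting sound records. The SD, r0 and the actual number of extra sessions used are assumptions.

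The paper-record example applies only to therapist contacts and costs that include them, and only if the CSRI counts the extra sessions and the electronic source does not. It does not show that total cost would be biased. This is an inexpensive improvement to the planned analysis; it does not invalidate the triangulation study.

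**What to change.** In the Triangulation study analysis:

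1. Before comparing therapist contacts, put the extra sessions on the same footing in both sources. Either add the paper-recorded sessions to the electronic count where they are not already there, or remove them from the CSRI count. Make sure they are counted once in the costing.
2. Beside each ICC, report the mean CSRI-minus-record difference in each arm and the between-arm contrast of that difference with a 95% CI. Consider this together with the ICC when judging whether records can replace patient report.

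The cost is a few lines of analysis. The session records are already due to be extracted, and both sources are already collected. The downside is precision: with about 19 to 25 per arm the intervals will be wide, so they should be read as descriptive and not as a pass/fail test.

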### Study objectives

The objectives of this study are the following:To assess the acceptability of, and compliance with, the rehabilitation programme amongst patients, carers and clinicians and the fidelity of its delivery and to identify any adverse events.To assess the feasibility of a future definitive RCT by assessing the number of eligible patients, monitoring recruitment and retention rates, exploring the willingness of patient participants to be randomised and the willingness of patients and carers to complete process and outcome measures.To produce means and standard deviations of the quantitative measures so that effect sizes can be calculated for planning the future RCT.To explore how the intervention creates change in self-efficacy and fear of falling as potential mediators for improving function.To explore the methodological issues for conducting an economic evaluation alongside a future RCT including identifying the most efficient way of measuring patient level costs and health benefits, programme costs and potential payer stakeholders.To explore the feasibility and quality of data on service use extracted from patient electronic records compared with patient reported outcome measures. If successful, replacing patient reported outcomes of service use with data collection by researchers and the NHS information technology (IT) staff for electronic records has potential to reduce participant burden in future studies (this is referred to as the triangulation study later in the paper).

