### Randomised feasibility study

#### Selection of subjects for randomised feasibility study

Of all those admitted, we anticipate that we will be able to identify and invite 150 patients (50% of a conservative estimate of the total) from the three hospital sites across BCUHB during the 6-month study period to participate in the embedded feasibility study comparing usual care with the enhanced rehabilitation package using a randomised design. We will attempt to recruit 50 patients to this randomised feasibility study. The number of eligible patients, the recruitment and retention rates and the number who completed the outcome questionnaires will be recorded. It will be important to determine whether random allocation to either intervention arm is acceptable to patients, carers and clinicians providing the service. The feasibility study will also be an opportunity to test a package of process and outcome measures, including economic measures, for the main trial and to inform the effect size for a future sample size calculation. These patients will also be recruited to a triangulation study which aims to compare the quality of data collected about service use from patient-reported outcome measures compared with extracting the same information from patient electronic records.

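### The triangulation study's only numerical benchmark, an ICC above 0.7, can be met while the two sources differ substantially in the level of service use

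*Protocol article*

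**What the plan says.** The section on the triangulation study of service use states the comparison: "The health service use data obtained from the patient completed CSRI questionnaires will be compared with the same information obtained from routinely collected data". The triangulation study analysis section covers discrete counts, such as GP and hospital visits, and "continuous variables such as medication and associated costs that will be compared for consistency". The method is an intraclass correlation coefficient (ICC), "with a value of above 0.7 showing good consistency between the two data sources". The section does not say which form of ICC is meant.

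The study objectives give the purpose: "If successful, replacing patient reported outcomes of service use with data collection by researchers and the NHS information technology (IT) staff for electronic records" is said to have the potential to reduce participant burden in future studies.

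On what the data are for, the health economic measures section says of the CSRI: "This information will be combined with national sources of reference unit costs". The economic analysis section adds service-use costs to the intervention cost and compares the resulting cost per QALY with a range of £20,000 to £30,000.

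On numbers, the plan says: "We will attempt to recruit 50 patients to this randomised feasibility study". The statistical analysis section sets 75% as the retention rate for feasibility.

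**The concern.** Multiplying contacts by unit costs makes mean cost proportional to mean recorded use. A source that counts 40% fewer contacts in a category therefore gives a cost 40% lower in that category. What an economic evaluation most needs to know about a substitute source is whether it has the right level.

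An ICC answers a different question. In its consistency form it discards an additive difference between sources altogether. A proportional shortfall lowers it only because the variance of the lower source shrinks, and that penalty is mild. In its absolute-agreement form a difference in level does lower the coefficient, but the difference is scaled against the spread between patients. Where use varies widely, as service use usually does, a large shortfall can still pass. Neither form reports how far apart the sources are or which is lower.

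At stake is the advice carried into the definitive trial: the sub-study could report good consistency for records that would cost the affected services well below what patients report.

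**Working it through.** **The plan's own figure.** The 0.7 is a chosen cut-off with no inputs, so there is nothing to reproduce. The check is what the cut-off lets through.

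**Inputs from the documents.** Cut-off 0.7; 50 recruited; 75% retention, so 0.75 × 50 = 37.5, about 38 pairs.

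**Assumptions (not in the documents).** CSRI contacts are negative binomial with mean m = 4 or 6 and dispersion parameter k = 3 or 6, so v = m + m²/k. The CSRI is error-free. Records capture each contact independently with probability c.

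**Formulas, two sources.** Record variance v₂ = c²v + c(1−c)m; covariance = cv; mean difference d = m(1−c).

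- Consistency ICC = 2cv / (v + v₂)
- Absolute-agreement ICC = 2cv / (v + v₂ + d²)

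**Worked case.** Take m = 6, k = 3, c = 0.6. Then v = 6 + 36/3 = 18, v₂ = 0.36×18 + 0.24×6 = 7.92, covariance = 10.8 and d = 2.4.

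- Consistency: 21.6 / 25.92 = 0.83
- Agreement: 21.6 / (25.92 + 5.76) = 0.68

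**All four combinations of m and k, with a more dispersed case (m = 6, CV = 1, so v = 36) added:**

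| Capture | Mean use too low by | Consistency, four cases | Agreement, four cases | Consistency, CV 1 | Agreement, CV 1 |
|---|---|---|---|---|---|
| 70% | 30% | 0.87 to 0.90 | 0.75 to 0.81 | 0.92 | 0.87 |
| 60% | 40% | 0.80 to 0.83 | 0.61 to 0.69 | 0.86 | 0.77 |
| 50% | 50% | 0.71 to 0.75 | 0.47 to 0.56 | 0.77 | 0.65 |

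Read as consistency, every row passes. Read as agreement, 70% capture always passes, 60% passes only in the more dispersed case, and 50% fails.

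**Sampling check.** In 4,000 simulated studies of 50 pairs (m = 6, CV = 1), 60% capture exceeded 0.7 in over 99% of runs under consistency and in 90% under agreement. At 50% capture the proportions were 92% and 16%.

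**Precision at the cut-off.** With two sources, F = (1 + 0.70)/(1 − 0.70) = 5.67. The limits are (F/q − 1)/(F/q + 1) and (Fq − 1)/(Fq + 1), where q is the 97.5% point of F on n−1 and n−1 degrees of freedom.

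- n = 38: q = 1.924, giving 0.49 to 0.83
- n = 50: q = 1.762, giving 0.53 to 0.82

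**Sensitivity to error in the CSRI.** If CSRI reliability is assumed to be 0.8, v is replaced by v/0.8 for the CSRI in the denominator. In the worked case, consistency becomes 21.6 / (22.5 + 7.92) = 0.71. Across the four cases, consistency is 0.68 to 0.71 at 60% capture and 0.75 to 0.77 at 70%. Agreement is 0.54 to 0.60 at 60% and 0.66 to 0.71 at 70%.

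**The case against.** **A replacement rule might be inferred, but none is stated.** A reader who joins the 0.7 cut-off to the words "If successful, replacing patient reported outcomes of service use with data collection by researchers" could conclude that the protocol accepts records automatically once the ICC exceeds 0.7. It does not say so. The objective is exploratory, replacement is described as a potential for future studies, and nothing equates success with the cut-off. What stands is that 0.7 is the only numerical benchmark offered for judging the comparison.

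**The ICC form is not named.** Consistency may be meant in its ordinary sense, and the form and its interval may be fixed in a document not shown. Their absence is therefore not the point. The point is that the stated benchmark is a poor guide under either form. It is weaker under absolute agreement, but 70% capture still passes when the CSRI is error-free.

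**The calculation favours the concern.** The CSRI is retrospective self-report, and treating it as truth raises the ICC. With CSRI reliability of 0.8, 60% capture becomes borderline under consistency and 70% becomes borderline under agreement, although 70% still passes under consistency. This limits the size of the claim but does not remove it.

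**It would be too much to say that every cost in the future trial would be biased.** Intervention costs are built separately from therapist band, time, travel and equipment. The CSRI also covers social and voluntary services, whereas the triangulation concerns health service use. Only categories actually taken from records would be affected. The ICC is also symmetric, so it cannot tell under-recording from over-reporting.

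**Conclusion.** The point holds as a weakness in the stated criterion. An ICC above 0.7 is not sufficient evidence that records and CSRI give the same level of service use. With an error-free CSRI and the assumed counts, a 40% shortfall passes comfortably under consistency (0.80 to 0.83). Under absolute agreement a 30% shortfall passes (0.75 to 0.87), and a 40% shortfall passes only where use is highly variable (0.77 at CV 1, against 0.61 to 0.69 otherwise). Capture rates, means and dispersions are all assumed, and error in the CSRI lowers these values. At 38 to 50 pairs, an observed value near the cut-off is compatible with anything from about 0.5 to just above 0.8.

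The consequence is confined to an exploratory sub-study and the advice it gives on the cost source for a later trial. The eligibility, recruitment and retention criteria and the Barthel analysis are untouched. The change is worth making because it costs almost nothing.

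**What to change.** In the triangulation study analysis section:

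1. Name the coefficient as a two-way, absolute-agreement, single-measure ICC, and report it with its 95% confidence interval.
2. For each service category and for total cost, report the signed mean difference (records minus CSRI), in contacts and in pounds, with its 95% confidence interval and limits of agreement.
3. State that any conclusion that records could replace the CSRI will rest on both the ICC and the mean difference, not on an ICC above 0.7 alone.
4. Note that a difference shows which source is lower, not which is wrong.

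Changing the ICC form without item 2 would not be enough, since a 30% shortfall can still pass. A fixed margin for an acceptable cost difference is optional; the documents give no basis for a value, so the study team would have to choose and justify one.

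The cost is a few lines of wording and a small amount of analysis on data already being collected. Some categories that would have been reported as consistent may no longer be.

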#### Statistics

##### Sample size

We estimate that we will recruit 25% of eligible patients with a proximal femoral fracture admitted to the three acute hospitals in BCUHB and randomise them to either the enhanced rehabilitation programme or usual care. In order to estimate the standard deviation of the primary outcome measure (Barthel index), which will be used in a power calculation for a future definitive RCT, with a high level of confidence a sample size of at least 50 participants completing the trial is advisable [55].

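### A raw-scale ICC above 0.7 can mislabel agreement on service-use counts: one extreme user can carry it, and a rarely used service can fail it

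*Protocol article*

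**What the plan says.** Under Triangulation study analysis, the Protocol article compares participants' own reports with computerised records. The variables include "discrete variables such as number of GP visits, number of hospital visits etc", together with medication and costs, which it treats as continuous. The method is fixed in one sentence: "This comparison will be completed using the intraclass correlation coefficient (ICC"), "with a value of above 0.7 showing good consistency between the two data sources". The form of the ICC, the scale of analysis and any second measure of agreement are not given.

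The sample is that of the feasibility study. Selection of subjects for randomised feasibility study says "These patients will also be recruited to a triangulation study" and "We will attempt to recruit 50 patients to this randomised feasibility study". Statistical analysis sets 75% as the retention needed. Sample size, on the other hand, says "a sample size of at least 50 participants completing the trial is advisable".

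The purpose is given under Study objectives: if the comparison succeeds, "replacing patient reported outcomes of service use with data collection by researchers" and NHS IT staff could reduce participant burden in future studies.

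**The concern.** An ICC is the share of the total variance that lies between people. Counts of service use commonly have many low values and a few high ones, so a few people can supply most of that variance.

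- **False pass.** One heavy user whom both sources record much alike creates a large between-person variance. The ICC can then be high even if the sources are unrelated for everyone else.
- **False fail.** For a service that almost nobody uses there is hardly any between-person variance, and one or two discordant records can pull the ICC below 0.7 although nearly all records match.

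At stake is the label given to each service, good consistency or not, and through it the advice on whether record extraction could replace patient report in later studies. The label could turn on one or two participants.

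**Working it through.** **Inputs from the article.** Cut-off 0.7; 50 recruits; 75% retention. The triangulation section states no sample size or precision. The article's retention bound reproduces with n = 50: 0.75 − 1.96 × √(0.75 × 0.25 / 50) = 0.75 − 0.12 = 0.63, the stated 63%. With 50 recruits and 75% retention, 0.75 × 50 = 37.5, so about 38 people have 3-month data. This figure is derived, not stated. Because Sample size speaks of 50 completing, both n = 38 and n = 50 are used.

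**Assumed inputs.** The article gives no distribution of service use. The Poisson means, heavy-user counts and rare-use tables below are assumptions.

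**False pass.** Let n − 1 people have independent Poisson counts with mean m in the two sources (true ICC 0), and let one person have H visits in both. That person adds about (H − m)²/n to the between-person variance, and the within-person variance is about m, so

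ICC ≈ [(H − m)²/n] / [(H − m)²/n + m].

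For m = 3, H = 25, n = 38: 22²/38 = 12.74, and 12.74/15.74 = 0.81. Simulation (two-way consistency ICC, 20,000 samples per row) agrees:

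| m | H | median ICC, n=38 | above 0.7, n=38 | median ICC, n=50 | above 0.7, n=50 |
|---|---|---|---|---|---|
| 3 | 12 | 0.43 | 0.3% | 0.36 | 0% |
| 3 | 15 | 0.57 | 5% | 0.50 | 0.4% |
| 3 | 20 | 0.73 | 67% | 0.67 | 29% |
| 3 | 25 | 0.82 | 99% | 0.77 | 93% |
| 2 | 10 | 0.47 | 0.7% | 0.40 | 0% |
| 2 | 20 | 0.82 | 99% | 0.77 | 93% |

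Setting the approximation to 0.7 gives H = m + √(7nm/3). At n = 38 that is about 10, 15, 19 and 23 visits for m = 1, 2, 3 and 4, or roughly 6 to 10 times the mean of the others. At n = 50 it is about 12, 17, 22 and 26.

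The two records of the heavy user need not be identical, but they must be close. At n = 38, m = 2 with 20 against 16 visits exceeds 0.7 in 87% of samples, while m = 3 with 20 against 15 does so in 14%.

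Two checks expose the false pass. Without the heaviest user the median ICC returns to about 0. On log(1+x) it is 0.27 for m = 3, H = 20 and 0.32 for m = 3, H = 25 at n = 38, and almost no sample exceeds 0.7.

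The consistency, absolute-agreement and one-way forms gave practically the same results, so naming the form would not remove the problem.

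**False fail.** Use of a service coded yes/no, n = 38:

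| users in both | patient report only | record only | agreement | ICC | kappa | agreement among those with use in either source |
|---|---|---|---|---|---|---|
| 1 | 1 | 0 | 97% | 0.66 | 0.65 | 1 of 2 |
| 1 | 1 | 1 | 95% | 0.47 | 0.47 | 1 of 3 |
| 2 | 1 | 1 | 95% | 0.64 | 0.64 | 2 of 4 |
| 2 | 1 | 0 | 97% | 0.79 | 0.79 | 2 of 3 |
| 3 | 1 | 1 | 95% | 0.72 | 0.72 | 3 of 5 |
| 0 | 1 | 1 | 95% | −0.03 | −0.03 | 0 of 2 |

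With the same percent agreement, the ICC falls on either side of 0.7 according to how many shared users there are. If nobody uses the service, the ICC is undefined. Kappa follows the ICC throughout.

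**Sampling error, for context.** For normal data an observed ICC of 0.70 has an F-based 95% confidence interval of 0.49 to 0.83 at n = 38 and 0.53 to 0.82 at n = 50. An interval alone does not cure the false pass. At n = 38 the lower limit exceeds 0.7 once the observed ICC is about 0.835, and m = 3 with one user at 30 visits gives a median of 0.87.

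**The case against.** The case against is substantial.

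- **Nothing binding rests on 0.7.** The objective is exploratory, success is not defined as an ICC above 0.7, and the triangulation is not among the criteria for a full trial (eligibility, recruitment, retention). This stands. A reader might infer that the cut-off formally decides whether records replace patient report, but the article does not say so. It fixes only the label.
- **Intervals and sensitivity analyses may sit in a fuller plan.** This stands too. The absence of a confidence interval from a journal article is no defect by itself. What the article does fix is one raw-scale cut-off for this kind of data.
- **The heavy-user case is extreme.** It assumes no relation at all between the sources in everyone else, and an outlier recorded much alike in both. It would be wrong to infer that any heavy user carries the ICC past 0.7: with a mean of 3, users at 12 or 15 visits rarely do.
- **Rare services do not always fail.** Correct: two of the six tables above pass. Where neither source confirms a use recorded by the other, a low ICC is a fair warning for costing, since the agreement consists only of shared zeros.
- **Kappa is no remedy.** Correct, as the table shows.

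These objections limit the size of the point. They do not make a single raw-scale cut-off a safe label for skewed counts in so few people.

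**Conclusion.** The point holds in a limited form. Reading a raw-scale ICC above 0.7 as good consistency can mislabel services in either direction. A false pass needs one extreme user, under these assumptions roughly 7 or more times the mean of the others (more at lower means), recorded much alike in both sources. The effect is weaker at n = 50 than at n = 38 but persists. A false fail is possible, not certain, for services with only one or two shared users.

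The sizes rest on assumed Poisson counts and on a sample of about 38 to 50. The data may be more or less skewed than this. The consequence is confined to an exploratory sub-study and to the advice drawn from it for future studies. The importance is minor to moderate.

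**What to change.** 1. For each count or cost, report the ICC, naming its form, with a 95% confidence interval: on the raw scale, on log(1+x), and with the heaviest user left out. Call consistency good only if that conclusion does not depend on the one participant.
2. For services used by few participants, do not apply the 0.7 cut-off. Give the cross-table of any use by source, with overall percent agreement and agreement among those with use in either source. The second figure is needed because the first is dominated by shared zeros. Do not rely on kappa, which behaves like the ICC at low prevalence.
3. Set in advance how few users make a service rarely used, so that the choice of method does not follow the result.

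The cost is some wording and a little more output, with no new data. The downside is that fewer services will be labelled good.
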